### Intervention – experimental group

A home-based self-management program based on behaviour change techniques will be implemented through the Social-Cognitive Theory [14] and Control Theory approaches [15]. According to these theories, a behaviour to achieve a goal is influenced by self-efficacy [14] and feedback [15]. In the present study, we will use the Behaviour Change Technique Taxonomy (v1) proposed by Michie et al. 2013 to standardise the way to report *behaviour change techniques* [16]. The intervention protocol was adapted from Preston et al. 2017 and will include six sessions of home-based self-management, with an average duration of sixty minutes [17]. The content, materials, and theoretical framework of each session are described in Table 2.

**Table 2 Tab2:** Intervention components, materials, theoretical framework and behaviour change techniques

Session	Components	Materials	Behaviour change technique (Theoretical framework)
**Session 1**	Education about stroke (what is, symptoms, risk factors, how to prevent another event)	Booklet “*Had a stroke, what now?*”	
**Session 2**	Feedback about initial measurement outcomes	Data from Actigraph (steps taken per day)	Feedback on behaviour (CT)
	Education about the consequences of physical inactivity	Booklet “*Consequences of physical inactivity*”	Health consequences (SCogT)
	Choose a target exercise	Exercise Preference Questionnaire	Action planning (SCogT)
	Generate a list of goals	Goal Attainment Scaling	Graded tasks (SCogT)
	Delivery self-monitoring devices	Smartband and paper-based exercise diary	Self-monitoring of behavior (CT)
**Session 3**	Review goals	Goal Attainment Scaling	Review behavior goal(s) (CT)
	Review strategies to self-monitoring	Smartband and paper-based exercise diary	Self-monitoring of behavior (CT)
	Encouraging	Verbal therapist encouragement	Non-specific encouragement (SCogT)
	Identify barriers and potential solutions	Exercise Benefits/Barriers Scale and paper-based barriers and solutions list	Problem-solving/coping planning (SCogT)
	Implementation of the physical exercise session with the participant	Paper-exercise guide	Instruction on how to perform a behaviour (SCogT)
	Development of a weekly schedule of physical exercise	Weekly activities calendar	Goal setting (behavior) (CT)
**Session 4**	Review goals	Goal Attainment Scaling	Review behavior goal(s) (CT)
	Review strategies to self-monitoring	Smartband and paper-based exercise diary	Self-monitoring of behavior (CT)
	Review weekly schedule physical exercise;	Weekly activities calendar	Goal setting (behavior) (CT)
	Encouraging	Verbal therapist encouragement	Non-specific encouragement (SCogT)
	Review barriers and potential solutions	Paper-based barriers and solutions list	Problem-solving/coping planning (SCogT)
	Vicarious experience	Paper-based stroke survivors report about the self-management program (data from feasibility study)	Vicarious reinforcement (CT)
**Sessions 5 and 6**	Review goals	Goal Attainment Scaling	Review behavior goal(s) (CT)
	Review strategies to self-monitoring	Smartband and paper-based exercise diary	Self-monitoring of behavior (CT)
	Review weekly schedule physical exercise	Weekly activities calendar	Goal setting (behavior) (CT)
	Encouraging	Verbal therapist encouragement	Non-specific encouragement (SCogT)
	Review barriers and potential solutions	Paper-based barriers and solutions list	Problem-solving/coping planning (SCogT)

Legend: *CT* Control Theory, *ScogT* Social-Cognitive Theory

Session 1 will include education about stroke (what it is, symptoms, risk factors, how to prevent another event, and orientation regarding the importance of practising physical activity after a stroke).

In Session 2, the therapist will provide feedback about sedentary behaviour and the consequences of physical inactivity. Then, the participants will choose a target exercise through the Exercise Preference Questionnaire [18] and generate a list of goals using the Goal Attainment Scale (GAS) [19]. They will be asked to set short, medium and long-term goals using the GAS. In the first moment, participants will be encouraged to set short-term goals that are important to them and with low difficulty levels. As soon as short-term goals are achieved, they will be encouraged to attain medium-term goals (medium difficulty levels). Finally, long-term goals (high difficulty levels) will be added when the medium-term goals are achieved. At the end of the session, self-monitoring devices will be provided to participants. The focus is to show participants that they can perform a behaviour and to help them achieve it by increasing self-efficacy [14] and providing them with support and feedback [15].

In Session 3, besides reviewing goals and self-monitoring strategies, the therapist will also verbally encourage all participants to motivate them to achieve a target behaviour. For those participants who completed the target behaviours, the therapist will say, “*You are doing well; let’s move on!”*. For those who have not achieved the behaviour, the therapist will say, “*Don’t give up; what can be changed for you to achieve this behaviour?*”. Then, barriers to exercise will be assessed by self-reporting and completing the Exercise Benefits/Barriers Scale [20]. The therapist, the family, and the caregivers will help each participant find solutions to the identified barriers. At the end of the session, the therapist will implement the first physical exercise session with the participant. In addition, a weekly schedule of physical exercise will be developed.

In Session 4, goals, self-monitoring strategies, and weekly physical exercise schedule will be reviewed. Barriers and potential solutions will be discussed, and verbal encouragement will be given as in the previous session. In addition, the therapist will provide a vicarious experience and show participants a paper-based report from the stroke survivors about the self-management program carried out in the previous feasibility study. This report will provide information on the barriers and benefits of this self-management program.

Sessions 5–6 will give the exact content of Session 4 except for vicarious experience.

The home-based self-management program will be delivered individually, in person, at the participant’s home, by a trained physical therapist (with knowledge of *behaviour change techniques*) over 11 weeks. The six sessions will be scheduled under the availability of the therapist and the participant’s schedule. The first three sessions will have a one-week interval between them. The following two sessions will occur at two-week intervals. Finally, the last visit will appear after a four-week break. Although the program has a standardised structure, some components of the intervention, such as choosing a target exercise, a list of goals in the GAS format, a paper guide to exercise, and a weekly physical exercise schedule, will be developed according to each participant. After exercise, participants will be asked to report any adverse events (falls, pain, etc.). To improve the recording of exercise over the feasibility study, self-monitoring devices (smartband and paper-based exercise diary) will be delivered to participants in Session 2 and will stay with them until Session 6.

Adherence to the home-based self-management exercise program will be measured by Section B of the Exercise Adherence Rating Scale [21, 22] collected at Week 11. The scores in this section range from 0 to 24; the higher the score, the higher the adherence. The answers to this scale will be based on participant self-report, reading both the smartband records and completing a paper-based exercise diary. To check adherence after the intervention, the therapist will also apply the Exercise Adherence Rating Scale at Week 24.

### Control group

The control group will receive one session of education about stroke (what it is, symptoms, risk factors, how to prevent another event, and orientation regarding the importance of practising physical activity after a stroke). This session will occur in the participant’s home, in person, on week 1, by the same therapist who will provide the intervention in the experimental group. In the subsequent weeks, they will receive usual care, which may include medical follow-up and guidance from other healthcare professionals (who are not involved with the research team) regarding the significance of behaviour change after stroke. It is a pragmatic study, so participants of both experimental and control groups will be allowed to perform daily living and healthcare activities (e.g., physiotherapy, occupational therapy, activities in a health centre, etc.).

### Primary outcome

A triaxial accelerometer will measure physical activity (Actigraph wGT3X-BT, Pensacola, FL, USA) [23]. Participants will be asked to wear the device on their waists and non-paretic sides [1]. They will be advised to wear the device during waking hours, except during water activities. The mean of steps taken per day over four days (two weekdays and two weekend days) will be recorded and reported in baseline (week 0), post-intervention (week 12) and follow-up (week 24) in both experimental and control groups. The mean of daily steps will be analysed to compare groups after intervention. As a way to describe the sample, the percentage of time spent in sedentary activities and moderate and vigorous physical activity will be reported at baseline, post-intervention, and follow-up in both groups. These data will not be used to compare groups after intervention. The Actigraph shows adequate psychometric properties in individuals after a stroke [23].

### Secondary outcomes

In the present study, we will change one questionnaire to reduce the time spent in this section. The Assessment of Life Habits Questionnaire (LIFE-H 3.1) [24], which measures social participation, will be replaced by the Stroke Impact Scale [25].

Cardiovascular risk will be measured according to the American College of Sports Medicine as body mass index (kg/m2), waist circumference (cm), and blood pressure (mmHg) [26].Depressive symptoms will be measured by the short version of the Geriatric Depression Scale [27]. The results will be reported in scores from 0 to 15, where scores ≥ 6 suggest the presence of depression [27]. This scale shows adequate psychometric properties in stroke [28].Walking ability will be measured by the distance covered in the 6-Minute Walk Test and by the habitual and maximum walking speed through the 10-Meter Walk Test. They will be implemented following previous recommendations [29]. These tests show adequate psychometric properties in stroke [30].Exercise Self-Efficacy will be measured through the Self-Efficacy for Exercise scale. The results will be reported in scores from 0 to 10, where 10 is the maximum self-efficacy [31]. This scale shows adequate psychometric properties in stroke [31].Social participation will be measured by the participation domain of the Stroke Impact Scale, the Brazilian version [25]. The results will be reported in percentage from 0 to 100%, where a higher percentage demonstrate better social participation levels. This scale shows adequate psychometric properties in stroke [25].Quality of life will be measured by the Brazilian version of EuroQual-5D [32]. The results will be reported in scores from 0–100, where higher scores demonstrate a better quality of life [32]. This scale shows adequate psychometric properties in stroke [32].

### Data monitoring body

The overall responsibility for the trial is under the supervision of [name]. The responsibility for stopping recruitment in case of several serious adverse events is under the control of [name]. She is a researcher who is not involved in the present study. She will receive reports on adverse events for each inclusion of 5 participants.

### Sample size estimate

The present study is a Phase II pilot clinical trial and a specific intervention in a particular sample [sedentary individuals (> 5,000 steps/day) and with mild walking disability (gait speed ≥ 0.8 m/s] will be developed. So, data from the mean and standard deviation required to produce a sample size are unavailable in the literature. So, in this case, a formal sample size calculation will not be undertaken. To estimate the number of participants required in the present study, we will follow the recommendations of Julious et al., who support that 12 subjects per group are enough for pilot clinical trials [33, 34].

### Statistical analyses

All analyses will be conducted intention-to-treat by a statistician blinded to group allocation. Descriptive analyses will be used as mean and standard deviation for parametric data and median and interquartile interval for non-parametric data. The analysis will include examining data distribution and variance equality to confirm the appropriate application of parametric analysis. Information from the latest available evaluation will be used for missed sessions. Two-way analyses of variance with repeated measures at the three-time points (baseline, post-intervention, and follow-up) will be implemented for all parametric outcomes to determine the statistical significance of the between-group differences and reported as mean differences between groups (95% CI) [35]. For non-parametric outcomes, the Kruskal–Wallis test will be used to determine the statistical significance of the between-group differences and reported as mean differences between groups (95% CI) [35]. Baseline characteristics judged clinically different between groups may be included as covariates and will be analysed using analysis of covariance (ANCOVA) and presented as mean differences between groups (95% CI) [35]. All analyses will be performed using the SPSS software (23.0 version).

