### Inclusion criteria

The inclusion criteria will be the same as those for the feasibility study. The only exception now is that we will only include sedentary participants, as the feasibility study showed they benefited most from the program. Therefore, the inclusion criteria are: (1) time since stroke less than six months (2) ≥ 18 years of age; (3) able to walk ten meters independently at a speed ≥ 0.8 m/s without any walking devices; [9] (4) no cognitive impairments (determined by the cut-off scores on the Brazilian version of the Mini-Mental State Examination); [10] (5) sedentary (mean of steps counts < 5,000 steps/day [11], over four days, determined by a triaxial accelerometer—Actigraph wGT3X-BT, Pensacola, FL, USA). The exclusion criteria are (1) other neurological diseases; (2) comprehensive aphasia (evaluated by simple motor command); [12] (3) any other conditions that would prevent participation (e.g., recent post-surgery or surgery scheduled, travel or further compromise that prevents the participant from staying in Belo Horizonte during the intervention period).

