### Data collection

Measurements will be collected in the hospital in Belo Horizonte City, Brazil, by trained researchers blinded to group allocation. Outcomes will be measured at baseline (Week 0), post-intervention (Week 12), and follow-up (Week 24) (see Fig. 1).

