**Fig. 1 Fig1:**
[figure not shown]
Design of the trial

The measurement sessions will be restricted to 45 min. In the feasibility study, the duration of this section was 1.5 h, and participants expressed that it was too long (which may have influenced some participants’ decision to withdraw). To address this issue, we changed one instrument that measures social participation and reduced this section. We followed the SPIRIT checklist [13] to describe our protocol (see attached). The attached SPIRIT table (see Table 1) explains the schedule of this study and when enrolment, intervention/control group sessions and assessments will occur.

**Table 1 Tab1:** Schedule of enrolment, intervention, and assessment

	**Enrolment**	**Allocation**	**Weeks**								**Close-out**
**TIMEPOINT**	**-t2 (1 week before data collection in week 0)**	**-t1 (1 day before data collection in week 0)**	**0**	**1**	**2**	**3**	**5**	**7**	**11**	**12**	**24**
Eligibility screen	X										
Information consent	X										
Allocation		X									

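### Carrying the latest evaluation forward puts pre-treatment steps into the Week 12 and Week 24 outcomes of early dropouts; any missing outcomes can then bias the group difference by an amount, and in a direction, not known in advance

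*Protocol article*

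**What the plan says.** The Statistical analyses section commits to intention-to-treat: "All analyses will be conducted intention-to-treat by a statistician blinded to group allocation". For missing data it gives a single rule: "Information from the latest available evaluation will be used for missed sessions". This is a stated choice, not a detail left for an analysis plan.

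The word for what is missed could suggest treatment visits. Only an outcome visit yields an evaluation, however, and the Data collection section uses the same word for outcome visits: "The measurement sessions will be restricted to 45 min".

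The features of the design that bear on the rule are:

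- Outcomes are taken at Weeks 0, 12 and 24 only (Data collection; Table 1).
- Eligibility requires a "mean of steps counts < 5,000 steps/day" (Inclusion criteria).
- For the primary outcome, "The mean of daily steps will be analysed to compare groups after intervention" (Primary outcome). The model is a two-way repeated-measures analysis of variance over the three visits (Statistical analyses).
- Research question (i) asks about benefit at both 3 and 6 months. The trial's purpose is to supply a power analysis for Phase III (Background).
- Twelve participants per group are planned, with no formal calculation (Sample size estimate).

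**The concern.** Only the Week 0 evaluation precedes Week 12. For anyone lost before Week 12, the rule therefore records a change of exactly zero at both outcome visits. For anyone lost between Weeks 12 and 24, it records no change over that interval, although whether the benefit lasts is part of the question.

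No change is not automatically a neutral assumption. Participants are less than six months after stroke, and both arms may receive physiotherapy and other care (Control group), so either arm may shift for reasons other than the programme.

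The filled values then enter the analysis of variance as if they had been measured. Both the estimated difference and the SD behind its confidence interval are affected, and these are what a Phase III calculation would draw on. With 12 per arm, each early loss replaces 1/12 = 8.3% of an arm's outcome data.

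**Working it through.** **The plan's own figure.** 2 groups × 12 = 24, as stated. This is a rule of thumb, with no effect, SD or dropout allowance behind it. Every input below other than 12 per arm is therefore an assumption.

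**Formula.** Let gE and gC be the mean changes from baseline that the arms would show in full. Let dE and dC be the shares lost before Week 12, with dropout unrelated to outcome. Carry-forward gives lost participants a change of zero, so the expected difference is

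(1 − dE)·gE − (1 − dC)·gC,

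and the bias is dC·gC − dE·gE.

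- Equal dropout d: the bias is −d·(gE − gC), which is toward zero when there is a true benefit.
- No change in controls (gC = 0) and a gain in the experimental arm: the bias is −dE·gE, so no pattern of losses inflates the effect.
- Both arms gaining: the bias is upward only if dC/dE exceeds gE/gC.

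**Set 1.** Assumed control gain 1,000 steps/day and SD of change 1,700. Coverage is from simulation of 12 per arm, analysed as change scores.

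| Lost, experimental v control | True difference | Carry-forward expectation | Bias | 95% CI coverage |
|---|---|---|---|---|
| 2 v 2 | 1,500 | 2,083 − 833 = 1,250 | −250 (−17%) | 95.4% |
| 3 v 1 | 1,500 | 1,875 − 917 = 958 | −542 (−36%) | about 91% |
| 1 v 3 | 1,500 | 2,292 − 750 = 1,542 | +42 (+3%) | 96.5% |
| 3 v 1 | 0 | 750 − 917 = −167 | −167 | about 95% |
| 1 v 3 | 0 | 917 − 750 = +167 | +167 | about 95% |

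In the 1 v 3 row with a true effect, the loss ratio of 3 only just exceeds gE/gC = 2,500/1,000 = 2.5, so the inflation is small.

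**Set 2.** Assumed gains 1,500 and 500 (true difference 1,000) and SD of change 1,500. Phase III size is per arm at 80% power and two-sided 5%; without missing data it is 36.

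| Lost, experimental v control | Carry-forward expectation | Phase III n per arm it would imply |
|---|---|---|
| 3 v 3 | 750 | 56 |
| 4 v 1 | 542 | 112 |
| 1 v 4 | 1,042 | 28 |
| 0 v 4 | 1,167 | 22 |

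Analysing only the observed values in these four cases gave 991 to 1,006, with coverage of about 95%. Under carry-forward, the 4 v 1 case had coverage of 89%. Over this and the related scenarios run at the same SD, carry-forward reduced the SD of change from 1,500 to roughly 1,380–1,450. With no true effect and both arms gaining 1,000, losing 4 from one arm only gave a type I error of about 9%.

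**Dropout related to outcome.** Suppose completers gain 1,500 and 500, dropouts would have declined by 1,000, and losses are 4 v 1. The true difference is (8×1,500 − 4×1,000)/12 − (11×500 − 1×1,000)/12 = 667 − 375 = 292. Carry-forward gives 1,000 − 458 = 542, an inflation.

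**Losses after Week 12.** If a share d′ of an arm is lost between the visits, the arm's Week 24 mean is shifted by d′ × (Week 12 change − Week 24 change). Where the experimental arm would have decayed, the rule removes that decay among its dropouts and so favours persistence.

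**The case against.** The strongest reply is that the harm is conditional and its size invented. Much of this stands.

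- A reader might infer that the rule is bound to be used. The article does not show that. Of the length of the feasibility study's measurement sessions it says only "which may have influenced some participants’ decision to withdraw", gives no dropout rate, and describes shortening the sessions from 1.5 h to 45 min in response. With no missing outcomes the rule does nothing.
- A reader might infer that the bias runs freely in either direction. Inflation needs change in the control arm combined with more control losses, or decline among experimental dropouts. The article allows co-interventions and recruits early after stroke, but nowhere states an expected change in controls.
- A reader might infer that every value carried from baseline is below 5,000. Table 1 places screening a week before Week 0, so a separately measured Week 0 value could be higher. It would still be pre-treatment, which is what matters here.
- A reader might infer that the confidence intervals fail generally. In Set 1 only the 3 v 1 case loses coverage materially. The spurious 167 steps is about 0.24 of the full-data standard error, 1,700 × √(2/12) = 694.
- The SD shrinks by about 3–8%. Sampling error alone, on 22 degrees of freedom, gives a 95% interval of 0.77 to 1.42 times the SD. The Discussion also asks for caution and rules out any change to clinical practice.

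These points limit the severity. They do not supply a reason for the rule: it imposes an assumption about the outcome under study, and the article does not justify it.

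**Conclusion.** The point holds as a weak analysis choice that should be fixed; the documents do not show a flaw that invalidates the trial. If Week 12 or Week 24 outcomes are missing, carry-forward biases the difference by dC·gC − dE·gE when dropout is unrelated to outcome. That is toward zero with equal dropout and a true benefit, and otherwise of a direction not known in advance. It also assumes persistence from Week 12 to Week 24 and treats filled values as data in the SD and confidence interval.

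Under the Set 1 assumptions a true effect of 1,500 becomes 1,250, about 960 or about 1,540, depending only on who is lost. These figures rest on assumed changes, SDs and loss counts, and on a change-score comparison standing in for the planned repeated-measures analysis. They show what the rule can do and do not predict what will happen in this trial.

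**What to change.** Delete the carry-forward sentence and replace it as follows.

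- **Continuous outcomes, including steps per day:** fit a likelihood-based mixed model for repeated measures with Weeks 0, 12 and 24 all as responses and the baseline means constrained equal between arms. Report the group differences at Weeks 12 and 24. Every randomised participant with a baseline value then stays in the allocated group, under a missing-at-random assumption. Entering baseline only as a covariate would not do this, because a participant lost before Week 12 would have no outcome row and would drop out of the model.
- **Outcomes sent to the rank test:** analyse observed values or use multiple imputation. The mixed model does not cover these. Using observed values alone leaves out those who are lost and needs the stronger assumption that loss is unrelated to outcome.
- **Optional:** one sensitivity analysis for data missing not at random.

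The cost is analysis wording and slightly more analysis work, with no new visits or data. Confidence intervals may be slightly wider, because missing values no longer count as observations.

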**Methods:**

A Phase II pilot randomised clinical trial with concealed allocation, blinded measurement, and intention-to-treat analyses will be carried out. The inclusion criteria will be individuals diagnosed with stroke, in the acute or subacute phase, with mild walking disability, sedentary, and no significant language impairment. The participants will be randomly allocated to the experimental or control group. The experimental group will receive six sessions of a home-based self-management program based on behaviour change techniques through the Social-Cognitive Theory and Control Theory over 11 weeks. The control group will receive one session of education about stroke (regarding the importance of practising physical activity after a stroke) and usual care. A total of 24 participants will be recruited. The primary outcome will be physical activity, measured through steps taken per day by an activity monitor (Actigraph wGT3X-BT, Pensacola, FL, USA). The mean of daily steps will be analysed to compare groups after intervention. Secondary outcomes will be cardiovascular risk (body mass index, waist circumference, and blood pressure), depressive symptoms (Geriatric Depression Scale), walking ability (6-Minute Walk Test and 10-Meter Walk Test), exercise self-efficacy (Self-Efficacy for Exercise scale), social participation (Stroke Impact Scale) and quality of life (EuroQual-5D). Two-way analyses of variance will be implemented for all parametric outcomes, and the Kruskal–Wallis test for non-parametric outcomes will be used to determine the statistical significance of the between-group differences and reported as mean differences between groups (95% CI). All analyses will be conducted intention-to-treat. All outcomes will be measured at baseline (Week 0), post-intervention (Week 12), and follow-up (Week 24). This pilot clinical trial was registered online at Clinical Trials under number NCT05461976 on 4^th^ April 2022.

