Recently, we demonstrated the feasibility of implementing a home-based self-management exercise program to promote physical activity among stroke survivors with mild walking disability in Brazil [1]. Therefore, a Phase II trial is required to test this program against a control group to provide a power analysis for a fully-powered Phase III clinical trial. However, the feasibility analysis raised several essential points. First, the results revealed that sedentary participants, i.e., fewer than 5,000 steps per day, derived the most benefit from the program. Second, 59% of eligible individuals did not receive medical clearance to participate. Third, the primary barriers to physical activity were lack of support, knowledge, and accessibility. Fourth, only 28% of participants consistently filled in the diaries with information regarding their adherence to the program. Lastly, participants expressed that the measurement sessions were too long. A Phase II pilot randomised trial will address these issues and, in addition, we will answer the following questions:

(i)In sedentary individuals with a mild walking disability after stroke, does a home-based self-management exercise program promote physical activity (i.e., number of steps taken per day) more than usual care at 3 and 6 months?(ii)Does any improvement in physical activity carry over to improvements in cardiovascular risk, walking ability, depressive symptoms, exercise self-efficacy, social participation, and quality of life?

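### The steps/day analysis makes baseline one of three outcome levels, does not say which term or visit gives the between-group difference, and leaves baseline adjustment optional

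*Protocol article*

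**What the plan says.** All references are to the protocol article.

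- **Model (Statistical analyses):** "Two-way analyses of variance with repeated measures at the three-time points (baseline, post-intervention, and follow-up) will be implemented for all parametric outcomes".
- **What it is for (same section):** "to determine the statistical significance of the between-group differences and reported as mean differences between groups (95% CI"). No model term, contrast or visit is named.
- **Covariates (same section):** "Baseline characteristics judged clinically different between groups may be included as covariates", by ANCOVA. Baseline steps are not a planned covariate.
- **Comparison wanted (Primary outcome):** "The mean of daily steps will be analysed to compare groups after intervention".
- **Study question (Background):** whether the program raises daily steps "more than usual care at 3 and 6 months".
- **Visits (Data collection):** "Outcomes will be measured at baseline (Week 0), post-intervention (Week 12), and follow-up (Week 24").
- **Size (Abstract, Sample size estimate):** "A total of 24 participants will be recruited", on the rule that "12 subjects per group are enough for pilot clinical trials". No SD, effect size or correlation is given.

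**The concern.** The question is about the difference at 3 and 6 months, after treatment. The model takes in a third time point, Week 0, which precedes the first session in Week 1. A two-way repeated-measures ANOVA offers two omnibus terms that involve group, and neither is the quantity asked for. The group term averages the group difference over all three visits. The group-by-time term tests whether the difference varies over visits, with 2 degrees of freedom, and yields a p-value but no mean difference.

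The baseline step count is collected on everyone and would normally be expected to predict later steps. The plan adjusts for baseline only if someone judges the groups different, and even then only says that it may. The estimator then depends on the data, and in a trial of 24 precision is lost that could be had at no cost.

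The trial exists to supply the power analysis for a Phase III trial, so the effect estimate and its interval are its main product. They should be defined without ambiguity.

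**Working it through.** **Plan's own figure.** 12 per group × 2 groups = 24, which agrees with the stated total. There is no power calculation to reproduce.

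**Notation.** d12 and d24 are the true group differences at Weeks 12 and 24. The difference at Week 0 is taken as 0, because no session is delivered before Week 1. (Table 1 places allocation one day before the Week 0 measurements, so this also assumes that knowing the allocation does not alter baseline steps.)

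**Step 1: what each candidate term estimates.** The group main effect has expectation (0 + d12 + d24)/3. The mean post-baseline effect is (d12 + d24)/2. Their ratio is 2/3 whatever the SD, the correlation or the time pattern. Relative to Week 12 alone, the pattern matters:

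| Pattern (d12, d24) | Main effect | Shortfall v mean post-baseline effect | Shortfall v Week 12 |
|---|---|---|---|
| Sustained (1, 1) | 0.667 | 33% | 33% |
| Halves (1, 0.5) | 0.500 | 33% | 50% |
| Vanishes (1, 0) | 0.333 | 33% | 67% |
| Grows (1, 1.5) | 0.833 | 33% | 17% |

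A simulation (20,000 trials, 12 per arm, correlation 0.6, true effect 0.80 SD at both visits) agrees. The mean estimate was 0.53 for the main effect, and 0.80 both for Week 12 minus baseline and for ANCOVA at Week 12.

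**Step 2: precision.** Assumptions, none from the document: SD 1 at every visit, one correlation ρ between all pairs of visits, two-sided 5% test, 12 per arm, effect of 1 SD at Weeks 12 and 24. With s = √(2/12) = 0.408, the standardised signals at ρ = 0.6 are:

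- Group main effect: 0.667 / (s × √((1 + 2ρ)/3)) = 0.667 / (0.408 × 0.856) = 1.91, power 45%.
- Week 12 minus baseline: 1 / (s × √(2(1 − ρ))) = 1 / (0.408 × 0.894) = 2.74, power about 74%.
- ANCOVA at Week 12: 1 / (s × √(1 − ρ²)) = 1 / (0.408 × 0.8) = 3.06. Power is 83% by formula and 81–82% by simulation, which also counts the small cost of chance baseline imbalance.
- Group-by-time F test (2 and 44 df): power 79%.

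The variance of the change contrast relative to ANCOVA is 2(1 − ρ)/(1 − ρ²) = 2/(1 + ρ), which is 1.25 at ρ = 0.6.

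**Step 3: range over the assumed correlation** (same 1 SD sustained effect, by formula):

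| ρ | Main effect | Interaction F | Week 12 change | Week 12 ANCOVA |
|---|---|---|---|---|
| 0.4 | 52% | 60% | 57% | 72% |
| 0.5 | 48% | 69% | 65% | 77% |
| 0.6 | 45% | 79% | 74% | 83% |
| 0.7 | 42% | 89% | 86% | 90% |

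If the effect halves by Week 24 (ρ = 0.6), the main effect has 28%, the interaction 66%, and Week 12 ANCOVA is unchanged.

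**The case against.** The strongest reply is that dilution is not a fact of this plan. The text names no term and speaks of differences in the plural. Read with the stated comparison after intervention and at 3 and 6 months, it fits visit-specific or change-from-baseline contrasts at least as well as the group main effect. On those readings nothing is diluted. **This stands.** A reader might infer that the reported effect will be one third too small, but the document does not say so.

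Second, on power the interaction comes close to ANCOVA when the effect is sustained and the correlation is 0.6 or 0.7. Interaction and change contrasts do use the baseline data. **This also stands.** The case against the interaction is mainly that it gives no estimate with an interval, and that it loses ground if the effect fades or the correlation is lower.

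Third, a reader might infer that a diluted effect would be carried into Phase III. At fixed SD, an effect shrunk to two thirds would inflate that sample by 1/(2/3)² = 2.25. But the Primary outcome section also commits to reporting mean daily steps by group at all three visits, and the analysis section plans SDs for parametric data. Undiluted visit differences could be worked out from these, so that harm is not established.

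Fourth, repeated-measures ANOVA with baseline as a level is a valid test, this is a small pilot that counsels caution, and details of contrasts are often left to a fuller document. **This only partly stands.** The three-level model and the optional covariate rule are stated text, not omissions, and a better-defined analysis is available from the same data. Restricting entry to fewer than 5,000 steps/day may also lower the baseline correlation and reduce the gain from adjustment. But the advantage of ANCOVA over a change contrast, 2/(1 + ρ) in variance under the equal-SD assumption, grows as ρ falls.

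**Conclusion.** The point holds as an unresolved choice of estimate and an avoidable loss of precision, not as a demonstrated bias. The stated model does not identify which quantity answers the study question:

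- **Group main effect:** one third below the mean post-baseline effect. This follows from arithmetic alone, given no true difference at Week 0. Against Week 12 the shortfall is 17% to 67% for the patterns tried.
- **Interaction:** no dilution, but no single mean difference with a confidence interval.
- **Change from baseline:** no dilution, but about 74% power against 82% for baseline-adjusted ANCOVA, under an assumed 1 SD effect, correlation 0.6, equal SDs and 12 per arm. The power figures move with those assumptions, as the range above shows.

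The imbalance-triggered covariate rule is a weakness under every reading, because it makes the adjusted estimate depend on a judgement made after the data are seen.

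**What to change.** Replace the repeated-measures sentence and the covariate sentence in Statistical analyses with a statement that:

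1. The primary comparison is the between-group difference in mean steps/day at Week 12, and the Week 24 difference is secondary.
2. Each is estimated with baseline steps/day as a prespecified covariate, either by ANCOVA at each visit or by a linear mixed model with Weeks 12 and 24 as outcomes and group, visit, group-by-visit and baseline steps as fixed effects.
3. Each is reported as an adjusted mean difference with 95% CI.
4. Covariates are fixed in advance and are not chosen by inspecting baseline imbalance.
5. Other continuous outcomes are analysed in the same way, each with its own baseline value.

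This changes wording only. It needs no extra data, visits or participants, and the planned software can fit these models.
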